### Sample size and power

In the health systems-level intervention group, it is estimated the baseline proportion of cases where an antibiotic is taken will be 12% [19, 23, 24, 30] and 76% of parents will report being very or extremely satisfied [29]. Given the cluster design and co-primary outcomes, the sample size calculation used an intraclass correlation coefficient (ICC) of 0.02 to 0.05 for within-clinic correlation and a two-sided test with alpha = 0.025 to account for multiple comparisons. A total sample size of 1,566 children will be required to provide 80% power to detect an absolute difference in antibiotic courses taken of between 8% (ICC = 0.02) and 11% (ICC = 0.05) and an absolute difference in the proportion of parents satisfied between 9% (ICC = 0.02) and 12% (ICC = 0.05) when comparing the two intervention groups. Based on preliminary data from the 33 participating clinics, it is estimated there will be 27,997 eligible children across the sites over 3 years. With a projected 16% enrollment rate and 7% attrition rate [46], up to 4,100 children could successfully complete the study, well-exceeding the enrollment target of 1,566 children.

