One such method for promoting engagement between parents and clinicians is through shared decision-making [2]. Shared decision-making is an approach whereby parents and clinicians come to mutual agreement upon a treatment strategy when there is uncertainty about the most effective treatment approach or differing opinions about the optimal treatment. Shared decision-making is typically facilitated with the use of a conversation aid designed to inform the decision-making between parents and clinicians with best available evidence. A prior study of shared decision-making for AOM found that its use resulted in a 20% absolute reduction in antibiotic use and a 17% absolute increase in parent satisfaction [29]. While shared decision-making interventions may be effective tools to facilitate watchful waiting management, they have not been successfully scaled to improve care for children with AOM. Like shared decision-making interventions, health systems-level interventions have also led to reductions in prescribing for AOM; [23, 24, 30] however, studies comparing the effectiveness of health systems-level interventions and shared decision-making, or their use in combination, are lacking. Such studies are essential to develop appropriate guidance on the most effective approaches to minimize antibiotic exposure for children with AOM. The present study will compare the effectiveness and implementation outcomes of two pragmatic, patient-centered interventions to promote use of watchful waiting: a health systems-level intervention alone or a health systems-level intervention combined with shared decision-making. Both intervention approaches aim to reduce antibiotic exposure for children with AOM while increasing parent engagement and satisfaction with their child’s care.

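### The detectable antibiotic differences of 8 and 11 points match only an increase from 12%; for the reduction the trial seeks, about 6 and 8 points are detectable

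*Protocol article*

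**What the plan says.** All the planning inputs are in the Sample size and power section of the protocol article. For the health systems-level arm, "it is estimated the baseline proportion of cases where an antibiotic is taken will be 12" per cent, and "76% of parents will report being very or extremely satisfied". The calculation uses an "intraclass correlation coefficient (ICC) of 0.02 to 0.05 for within-clinic correlation" and "a two-sided test with alpha = 0.025 to account for multiple comparisons". It concludes: "A total sample size of 1,566 children will be required to provide 80% power" for "an absolute difference in antibiotic courses taken of between 8% (ICC = 0.02) and 11% (ICC = 0.05"), and for "an absolute difference in the proportion of parents satisfied between 9% (ICC = 0.02) and 12% (ICC = 0.05").

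No direction is attached to either difference, and no rate is given for the hybrid arm. The direction of interest has to be taken from elsewhere. The Background says "Both intervention approaches aim to reduce antibiotic exposure for children with AOM", and cites an earlier study in which shared decision-making, the component added in the hybrid arm, lowered antibiotic use by 20 percentage points. The Discussion repeats the aim of reducing unnecessary antibiotic use.

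**The concern.** At a reference rate as low as 12%, the detectable difference depends strongly on direction. Binomial variance shrinks as the rate falls towards zero and grows as it rises towards 50%, so a given number of children can detect a smaller fall than rise. A single undirected figure therefore cannot be the 80%-power difference both ways.

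Read as reductions, the stated differences take the hybrid arm to 4% (12 − 8) or to 1% (12 − 11). The second would mean almost no child taking an antibiotic, which is implausible as the smallest effect that the trial can detect with 80% power. This suggests that the figures were computed upwards from 12%.

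At stake is how a co-primary result is read. A reader using 8 to 11 points as the trial's sensitivity would think a true reduction of 6 or 7 points was largely out of reach. A null result would then be judged against the wrong yardstick.

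**Working it through.** **Inputs.** Reference rate 12%, N = 1,566, two-sided alpha 0.025, 80% power, ICC 0.02 and 0.05 (Sample size and power); 33 clinics (Abstract; Study setting and population). The allocation ratio is not stated, so 1:1 is assumed.

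**Effective sample size.** Mean clinic size m = 1,566/33 = 47.45. Design effect = 1 + (m − 1) × ICC.
- ICC 0.02: 1 + 46.45 × 0.02 = 1.929; 783/1.929 = 405.9 effective children per arm.
- ICC 0.05: 1 + 46.45 × 0.05 = 3.323; 783/3.323 = 235.6 per arm.

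**Detectable difference.** Solve |p1 − p2| = (2.241 + 0.842) × √[(p1q1 + p2q2)/n] with p1 = 0.12, for p2 above and then below 0.12.

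*Increase, which reproduces the plan's figures:*
- ICC 0.02, p2 = 0.1988: 3.083 × √[(0.1056 + 0.1593)/405.9] = 0.0788.
- ICC 0.05, p2 = 0.2264: 3.083 × √[(0.1056 + 0.1751)/235.6] = 0.1064.

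*Reduction:*
- ICC 0.02, p2 = 0.0586: 3.083 × √[(0.1056 + 0.0552)/405.9] = 0.0614.
- ICC 0.05, p2 = 0.0431: 3.083 × √[(0.1056 + 0.0412)/235.6] = 0.0770.

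With the pooled variance under the null hypothesis, the increases are 7.9 and 10.7 points and the reductions 6.2 and 7.7.

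| | ICC 0.02 | ICC 0.05 |
|---|---|---|
| Stated | 8 | 11 |
| Increase from 12% | 7.9 | 10.6 to 10.7 |
| Reduction from 12% | 6.1 to 6.2 | 7.7 |

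**Power at the stated differences (pooled variance).**
- 12% v 20%, ICC 0.02: 80.9%. 12% v 23%, ICC 0.05: 81.9%.
- 12% v 4%, ICC 0.02: 97.6%. 12% v 1%, ICC 0.05: 99.6%.

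At the same clinic size, 80% power for those two reductions would need about 2 × 218 × 1.929 = 841 and 2 × 95 × 3.323 = 631 children (218 and 95 being the per-arm numbers without clustering). A beta-binomial simulation with a t-test on clinic proportions agrees: 97% and 99.9% for the two reductions, 79% for each increase.

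**Sensitivity of the reduction figures.**
- Arcsine: 6.1 and 7.6.
- Continuity correction: 6.3 and 8.0.
- t reference with 31 degrees of freedom: 6.4 and 8.0.
- N after the 7% attrition (1,456): 6.3 and 7.8.
- Clinic-size coefficient of variation (CV) 0.4, design effect 1 + [(1 + CV²)m − 1] × ICC: 6.4 and 8.1.

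The range is thus about 6.1 to 6.4 and 7.6 to 8.1 points.

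**Could 8 and 11 be reductions under some other method?** A CV of about 1.33 gives reductions of 8.0 and 10.6. The same CV makes the detectable increase in satisfaction from 76% equal to 11.4 and 15.6 points, against the stated 9 and 12. A CV near 0.4 comes close to all four stated figures, with both outcomes computed upwards: 8.2 and 11.4 for antibiotics, 8.9 and 11.5 for satisfaction. No variant tried gave reductions of 8 and 11 while also fitting satisfaction.

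**The case against.** The strongest defence is that the sentence names no direction and specifies a two-sided test. The larger of the two directional values is then a safe bound: at 8 and 11 points, power is at least 80% whichever arm does better (about 81% to 82% upwards, 98% or more downwards). Read that way, the sentence is true, and this stands. But the bound is loose for the direction of interest, and nothing in the text presents it as a bound.

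A reader might go further and infer that the trial was powered for harm from the hybrid arm, against its own stated hypothesis. The documents do not support that. They never mention 20% or 23%, and never say the hybrid arm is expected to be higher. The Background sentence on aims describes both arms, so a reduction with hybrid relative to health systems-level is an inference, though a fair one given the cited effect of shared decision-making and the Discussion. Nor does the mismatch mean too little power; it runs the other way.

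It is also fair that the method is not fully known. The article gives no formula, allocation ratio or allowance for unequal clinic sizes. The plain formula gives 11.0 points for satisfaction at ICC 0.05 where the plan states 12. The reduction figures are therefore given as ranges and not as the plan's exact corrected values.

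**Conclusion.** The point holds as a misstated detectable difference for a co-primary outcome. For a reduction from 12%, the stated figures exceed the plain-formula (pooled) values by about 1.8 points at ICC 0.02 (8 − 6.2) and 3.3 points at ICC 0.05 (11 − 7.7). The error is conservative: on these inputs the trial can detect smaller reductions than it claims, and N = 1,566 is adequate for this outcome.

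The conclusion rests on the 12% reference rate, 33 clinics, 1:1 allocation and the stated ICCs, alpha and power. That the figures match only an increase does not depend on the choice among the standard formulas. The exact size of the detectable reduction does, within the ranges given. If 12% was not the rate actually used, the reduction figures change.

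**What to change.** In the sample-size section, state the direction and both rates (health systems-level to hybrid) at each ICC. Restate the detectable reduction from 12% as about 6 points (to about 6%) at ICC 0.02 and about 8 points (to about 4%) at ICC 0.05, naming the formula and any allowance for unequal clinic sizes. If a different reference rate lies behind 8 and 11 points, state it and recompute. The cost is a sentence or two; sample size, tests and design stay as they are.

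### 1,566 is given both as the number needed for 80% power and as the enrolment target despite 7% expected attrition; if enrolment stops there, about 1,456 children have outcomes

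*Protocol article*

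**What the plan says.** All the wording at issue is in one paragraph of the protocol article, under Sample size and power.

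- The requirement: "A total sample size of 1,566 children will be required to provide 80% power". It is calculated with "a two-sided test with alpha = 0.025 to account for multiple comparisons" and an "intraclass correlation coefficient (ICC) of 0.02 to 0.05 for within-clinic correlation".
- The supply: "it is estimated there will be 27,997 eligible children across the sites over 3 years".
- The losses: "With a projected 16% enrollment rate and 7% attrition rate", from which "up to 4,100 children could successfully complete the study".
- The comparison that closes the paragraph: "well-exceeding the enrollment target of 1,566 children".

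Table 1 gives the survey at day 10 as the only source of both co-primary outcomes (antibiotic taken, parent satisfaction). The section on patient eligibility, enrollment and data collection places that survey ten days after enrolment.

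**The concern.** A number required for power is a number analysed. An enrolment target is a number recruited. With 7% attrition between the two they cannot be equal, yet both are printed as 1,566. The last sentence also sets children who complete against a target expressed in children enrolled, so its two sides are in different units.

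Attrition bears directly on the primary analysis. A child without the day-10 survey has neither co-primary outcome, and the multiple imputation mentioned in the formative evaluation section concerns missing predictors. An enrolment target is a natural point at which to close recruitment. A team that takes the printed label at face value would close with fewer outcomes than the same paragraph says are needed.

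**Working it through.** **Inputs from the article.** N = 1,566; 33 clinics; two-sided alpha 0.025; ICC 0.02 and 0.05; 12% antibiotic taken and 76% satisfied in the health systems-level arm; detectable differences of 8 and 11 points (antibiotic) and 9 and 12 points (satisfaction); 27,997 eligible; 16% enrolment; 7% attrition.

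**Assumptions, not in the article.** 1:1 allocation, equal clinic sizes, and a two-proportion z test with a design effect. The antibiotic difference is taken as an increase from 12%, because only that direction comes close to the stated 8 and 11 points.

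**Step 1: the feasibility figure.** 27,997 × 0.16 = 4,480 enrolled, and 4,480 × 0.93 = 4,166 completers, printed as up to 4,100. The 4,100 is therefore already net of attrition.

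**Step 2: attrition applied to the target.**
- Enrol 1,566: 1,566 × 0.93 = 1,456 with outcomes, a shortfall of 1,566 − 1,456 = 110.
- Need 1,566 outcomes: 1,566 / 0.93 = 1,684 to enrol, which is 118 more.

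**Step 3: the stated power.** Children per clinic m = N/33; design effect DE = 1 + (m − 1) × ICC; effective number per arm n = (N/2)/DE; power = Φ[(d − 2.241 × s0)/s1]. Here d is the difference, s0 = √[2p̄(1 − p̄)/n], and s1 = √{[p1(1 − p1) + p2(1 − p2)]/n}.

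For 12% v 20% at ICC 0.02:
- N = 1,566: m = 47.45, DE = 1.929, n = 405.9, s0 = 0.02573, s1 = 0.02558. Power = Φ(0.873) = 80.9%, which reproduces the stated 80%.
- N = 1,456: m = 44.12, DE = 1.862, n = 390.9, s0 = 0.02622, s1 = 0.02607. Power = Φ(0.814) = 79.2%.

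All four stated scenarios, with the difference detectable at 80% power:

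| Scenario | Power, N = 1,566 | Power, N = 1,456 | Detectable, N = 1,566 | Detectable, N = 1,456 |
|---|---|---|---|---|
| Antibiotic 12% v 20%, ICC 0.02 | 80.9% | 79.2% | 7.9 points | 8.1 points |
| Antibiotic 12% v 23%, ICC 0.05 | 81.9% | 81.0% | 10.7 | 10.9 |
| Satisfaction 76% v 85%, ICC 0.02 | 84.2% | 82.6% | 8.6 | 8.7 |
| Satisfaction 76% v 88%, ICC 0.05 | 87.8% | 87.0% | 11.0 | 11.1 |

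The antibiotic figures match the article. The satisfaction figures come out somewhat more favourable than stated. In every row the two detectable differences round to the same whole point.

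**Step 4: why the loss is small.** The number of clinics is fixed at 33, so losing 7% of children shrinks the clusters and lowers the design effect. At ICC 0.02 the effective number per arm drops from 405.9 to 390.9 (3.7%). At ICC 0.05 it drops from 235.6 to 230.7 (2.1%).

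**The case against.** The strongest reply is that the plan is sound and one word is wrong. The paragraph does apply attrition, and it compares the net figure of about 4,100 with 1,566. That comparison makes sense if 1,566 counts children with outcomes, which also fits the sentence on the number required. It is also possible that 1,566 already allows for loss. The stated differences cannot settle the matter, because they round to the same whole points at 1,566 and at 1,456.

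Much of this stands. A reader might infer that the trial will not deliver the size it needs, or that it is materially underpowered. The article supports neither. It sets no rule closing recruitment at 1,566, it projects about 4,480 enrolments, and even the least favourable reading costs only 1 to 2 points of power. The single result below 80% also depends on direction: for a reduction from 12%, which is what the trial aims at, power at 1,456 is 97.1% (12% v 4%, ICC 0.02) and 99.6% (12% v 1%, ICC 0.05). Nor is there a faulty multiplication, since the projection of completers is correct apart from being rounded down.

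The label itself is not defended by any of this. If 1,566 means children with outcomes, it is not the enrolment target. If it means children enrolled, then either the required number will not be analysed, or attrition is already included and the number required is smaller than printed. This is not detail left to a fuller document, because the article prints both labels and the attrition rate itself.

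**Conclusion.** The point holds as a minor inconsistency: one figure carries two meanings that 7% attrition keeps apart. Its size is conditional. If enrolment stops at the printed target, about 110 outcomes (7%) are missing and power falls by about 1 to 2 points. The 8-point antibiotic scenario at ICC 0.02 goes to about 79%, and the other three stay above 80%. The more likely intention is that 1,566 is the number with day-10 outcomes and that only the label is wrong.

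The power figures rest on 1:1 allocation, equal clinics, the normal approximation and an antibiotic effect counted as an increase from 12%. A t reference with 31 degrees of freedom lowers power at both sizes; for satisfaction at ICC 0.02 it gives 81.1% and 79.5%. The change due to attrition stays about the same. Clinics of unequal size would also lower power at both sizes, but that is a separate matter.

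**What to change.** Change one sentence under Sample size and power, in one of two ways.

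1. State that 1,566 is the number of children with day-10 outcomes, and give the enrolment target as about 1,684 (1,566/0.93). If 1,566 had been taken as the enrolment limit, this adds 118 children, within the roughly 4,480 projected. If 1,566 was always meant as completers, it costs only the wording.
2. Keep 1,566 as the number enrolled, and restate power for about 1,456 analysed: about 79% for the 8-point antibiotic difference at ICC 0.02. The printed whole-point differences can stay.

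The first is preferable because it keeps the stated 80% power and puts both sides of the closing comparison in completers. The article says recruitment had not begun, so on that footing either change needs only wording, plus the revised target under the first.

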## Discussion

It is essential to develop interventions to optimize the management of children with AOM to reduce unnecessary antibiotic exposure, along with its inherent risks, and increase parent satisfaction with their child’s treatment. A watchful waiting management strategy for AOM offers a key opportunity to reduce antibiotic use for children with AOM; however, to date there have been no studies comparing the effectiveness of interventions to promote use of watchful waiting and parents’ perceptions and satisfaction with this approach. This study aims to fill the gap by evaluating the effectiveness and implementation outcomes of two pragmatic, patient-centered interventions – a health systems-level intervention with and without shared decision-making – that aim to reduce unnecessary antibiotic use for children with AOM while increasing parent satisfaction with their child’s care.

The strengths of this study include the cluster-randomized design, the mixed methods approach to guide implementation and evaluate outcomes and sustainability, and the diversity of the participating clinic systems. Additionally, components of the interventions are pragmatic and utilize tools that are freely available and feasible to implement in resource-limited settings. Another strength of the study is the use of surveys to accurately ascertain whether a prescribed antibiotic was actually filled and taken and to assess parent satisfaction with care. Given the pragmatic nature of the study, limitations will include the inability to assess whether included children who are diagnosed with AOM in clinical practice meet strict diagnostic criteria for AOM, the inability to assess the long-term sustainability of the intervention on prescribing practices, and the inability to determine the effects of changes in prescribing on antibiotic resistance. Nevertheless, this study will represent a significant contribution to the pediatric AOM literature where large, randomized, comparative effectiveness studies are lacking. It will provide a framework for other healthcare systems to reduce unnecessary antibiotic prescribing for AOM, engage parents and increase satisfaction with their child’s care, and inform national antibiotic stewardship policy development.

For further information about this study, please visit https://clinicaltrials.gov/study/NCT06034080.

## Data Availability

No datasets were generated or analysed during the current study.
